### Consent

Eligible participants (those who score 8+ on the AUDIT) will have the study explained to them by the detention officer or drug and alcohol worker and will be given an information leaflet about the study. Participants will be given as much time as they require to decide whether or not they want to take part in the study. If the arrestee decides to take part, written informed consent will be obtained. Any arrestee will be informed that they can refuse to participate without giving a reason for doing so, and anyone who has already consented can withdraw from the study at any time and does not need to give a reason for doing so. All consent forms include a box for arrestees to tick which gives their permission for the research team to look at their Police National Computer (PNC) and arrest data. All consent forms will be kept in a secure place at each police custody site until collected by a study researcher.

### Measures

The key outcomes measures in this pilot trial will be the percentage of eligible participants recruited and percent of enrolled participants retained at 12 months. Due to uncertainty about the mobility and traceability of our study population, the 6-month follow-up will enable us to re-check contact details and assess interim attrition.

In addition, we will administer a number of tools to assess response variability in key measures likely to be used in a future definitive trial. AUDIT score has been found to be responsive to change following alcohol intervention [26] and has been successfully used as an outcome measure in a recent trial with offenders [19]. Thus, AUDIT will be used to measure changes in alcohol consumption and risk status following brief intervention. In addition, we will use the modified Readiness to Change Ruler [27] to assess readiness to change drinking behaviour on a numerical scale of 0–10 and the EQ-5D to measure Quality of life [28]. We will also collect demographic data including age, gender, ethnicity and postcode, as well as the reason that the individual was arrested and subsequently whether the arrestee was charged or released without charge. Permission will be sought from participants at baseline for linkage to a) police force arrest data in order to validate self-report arrest data and b) PNC data in order to record and validate conviction and offending history and identify offences in 12 months after recruitment.

### Follow-up

Participants will be followed up by the project researchers at 6 and 12 months post-intervention. This will be by telephone or in person depending on the participant’s preference. At both follow-up points, all tools used at baseline will be repeated. At both 6 and 12 months follow-up, the AUDIT will cover the last 6 months. At both follow-up points, we will measure alcohol-related problems via the brief Alcohol Problems Questionnaire (APQ) [29,30] and collect data on health and social care resource costs via the modified short Service Use Questionnaire (S-SUQ) in preparation for future economic evaluation (UKATT [31]).

### Sample size

This is a feasibility pilot trial and not an outcome evaluation; therefore, a formal power calculation is not required [32]. However, providing data that can inform the power calculation of a definitive trial is an important function of a pilot study; a minimum number of 30 participants per study arm (90 in total) at 12 months is recommended to estimate a parameter for this purpose [33] (Figure 1). Whilst this study involves cluster rather than individual randomisation, the relatively small average cluster size means that no major adjustment to the value cited by Lancaster et al. [33] is required. Specifically, assuming that around 30 detention officers or drug and alcohol workers are randomised and using an intra-cluster correlation coefficient of 0.04, the design effect would be 1 + [(90 / 30) −1] × 0.04 = 1.08.

**Figure 1 Fig1:**
[figure not shown]
**Recruitment flowchart.**

Based on Brown et al. [11], we estimate that 59% of screened arrestees will score 8 or more on the AUDIT and of these, 33% will consent to participate in the study. We have assumed a conservative follow-up rate at 12 months of 50%. Detention officers or drug and alcohol workers in this pilot trial will need to approach 300 arrestees per arm, 900 in total. With nine police custody sites across the two geographical areas in this study, hence, each site will need to approach around 225 arrestees over a 4-month period or approximately 56 per month. Success criteria will be to successfully recruit and deliver interventions to 60 participants per condition (180 in total) and follow-up at least 50% of these individuals at 12 months (90 in total). To minimise attrition during training, detention officers and drug and alcohol workers will be encouraged to obtain detailed participant contact details (particularly telephone numbers or email addresses) to enable follow-ups to take place with minimal difficulty.

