Key barriers to carrying out alcohol research in this setting include the busyness of custody settings, time constraints for police officers and acceptability of interventions to arrestees. However, a recent mixed-method study of screening and brief alcohol interventions in a policing context provided some evidence for the feasibility of a controlled trial [11]. Screening and brief alcohol interventions were delivered for 3 months by detention officers, during finger-printing procedures, and this input appeared to be acceptable to the majority of arrestees since 77% agreed to be screened and 98% of those screening positive consented to brief alcohol intervention [11]. Nonetheless, whilst all detention officers in one police station were successfully trained to deliver study interventions, they reported mixed views about the experience with just half the officers expressing enthusiasm for the role of delivering brief interventions in this setting [11]. Additional exploratory work by Coulton et al. reported that the majority of English offenders (74%) in police, prison and probation settings did not feel coerced into participating in screening and brief intervention activity [21]. In one sub-urban area of France, forensic physicians, described as addiction specialists, reported high rates of substance use in the police custody setting and concluded that intervention delivery was feasible because arrestees seemed responsive to brief intervention input [22]. The perspectives of the arrestees were not reported. Consequently, it is necessary to establish views from both arrestees and routine police staff about the acceptability of screening and brief alcohol interventions in this setting. In addition, work in this field needs to be scaled up to a larger number of police stations and to a wider geographical area to establish the grounds for a definitive multi-site trial.

The MRC has presented a framework for the development and evaluation of complex interventions [23]. This present work represents the development and piloting phases of this framework. Consequently, we propose a pilot feasibility trial, including a specified comparator condition, in two areas of England involving multiple police stations.

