### Screening

Following informed verbal consent, screening will be carried out by participating detention officers or drug and alcohol workers using the 10-question Alcohol Use Disorders Identification Test (AUDIT) [12]. Based on alcohol consumption during the previous 6 months, participants who score 8+ on the AUDIT (score range 0–40) will be eligible for the trial and asked to provide informed written consent. A score of 8+ indicates hazardous (score of 8–15), harmful drinking (16–19) or probable dependent drinking (20+) [12]. It is anticipated that screening will take place during routine processing, whilst fingerprints and other details are taken in the North East or during assessment in the South West. Routine processing is the last procedure to take place before an arrestee leaves custody; this means arrestees have to be suitably fit to be released and will be sober when screening takes place.

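### The 300 per arm (900 in total) given as arrestees to approach is really a number to screen: it allows for no refusal of screening, though the source study had 77% uptake

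*Protocol article*

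**What the plan says.** The relevant text is in the Sample size section of the protocol article, in the paragraph after the recruitment flowchart (Figure 1). Citing an earlier custody-suite study (reference 11), it estimates that "59% of screened arrestees will score 8 or more on the AUDIT and of these, 33% will consent". It assumes 50% follow-up at 12 months and concludes that staff "will need to approach 300 arrestees per arm, 900 in total". The target is 60 recruited per condition (180 in total), with half of them (90) followed up at 12 months. The same paragraph gives a workload of about 225 approaches per site over 4 months, with nine sites.

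Two other places bear on the step from approach to screening:

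- The Background reports that in the same source study "77% agreed to be screened and 98% of those screening positive consented to brief alcohol intervention".
- The Screening section makes screening conditional on agreement: "Following informed verbal consent, screening will be carried out by participating detention officers or drug and alcohol workers".

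Written consent to the trial is a separate, later step, taken from those who score 8 or more (Screening and Consent sections).

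**The concern.** The 59% has screened arrestees as its denominator, and the 33% has those who screen positive. Neither covers people who are approached and decline screening. The sample size text nevertheless multiplies these rates by a number labelled as approached. It gives no rate for the step from approached to screened, although the source study supplies one.

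The figure is used to plan staff workload and expected recruitment. If sites work to 900 approaches and some arrestees decline screening, expected recruitment falls below 180 even when every other assumption holds. Expected follow-up then falls below the 30 per arm (90 in total) that the Sample size section cites as the recommended minimum at 12 months. The pilot is also meant to report eligibility, consent and participation rates, so approached and screened need to be kept apart.

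**Working it through.** **Inputs**

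- Approached: 300 per arm, 900 in total (Sample size).
- AUDIT 8 or more among those screened: 0.59 (Sample size).
- Consent among those scoring 8 or more: 0.33 (Sample size).
- Follow-up at 12 months: 0.50 (Sample size).
- Agreement to screening in the source study: 0.77 (Background). Its use here is an assumption.

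**Reproducing the plan's figure**

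- Per arm: 300 x 0.59 x 0.33 = 58.4, against 60.
- In total: 900 x 0.59 x 0.33 = 175.2, against 180.
- In reverse: 60 / (0.59 x 0.33) = 308 per arm, and 180 / (0.59 x 0.33) = 924 in total.

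These agree with the stated 300/900 and 60/180 to within 3%, which is rounding. The plan's figure is therefore the two-rate product with no screening refusal.

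**Adding the screening step at 77%**

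- Screened per arm: 300 x 0.77 = 231.
- AUDIT 8 or more: 231 x 0.59 = 136.
- Recruited: 136.3 x 0.33 = 45.0 per arm; 900 x 0.77 x 0.59 x 0.33 = 134.9 in total.
- Followed up at 12 months: 45.0 x 0.50 = 22.5 per arm, about 67 in total.
- Approaches needed for 60 per arm: 60 / (0.77 x 0.59 x 0.33) = 400; for 180 in total, about 1,200.

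**Range over screening uptake**

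| Uptake | Recruited from 900 approached | Approaches needed for 180 |
|---|---|---|
| 70% | 123 | 1,321 |
| 77% | 135 | 1,201 |
| 85% | 149 | 1,088 |
| 90% | 158 | 1,027 |
| 100% | 175 | 924 |

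**Per-site figure**

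- 225 x 9 = 2,025, which is neither 900 nor 1,200.
- 900 / 9 = 100 per site (25 per month over 4 months); 1,200 / 9 = about 133 per site.
- 225 = 900 / 4, so the figure looks like a division by four rather than by nine.

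**The case against.** Several points on the other side have weight.

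*The word approach may simply mean screen.* This is possible in a condensed article, and then 300/900 stands as a number screened. But the wording would still need correcting, and the true approach workload would be stated nowhere in the text.

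*The 77% need not carry over.* This stands. The pilot covers more sites, a second region and, in some sites, different staff. The planners did not copy the source study wholesale either: it had 98% consent to intervention, while the plan uses 33% for trial consent. So 135 is one value in a range. The 33% cannot be read as absorbing screening refusals, however, because the text applies it to people who have already scored 8 or more.

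*The 225 per site leaves ample room.* Taken literally, 2,025 approaches at 77% uptake would give 2,025 x 0.77 x 0.59 x 0.33 = about 304 recruits. But 225 per site contradicts the 900 in the preceding sentence, so it cannot be taken as a deliberate allowance for refusals.

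*The flowchart may show the stages.* It is not available here. Since 300 already reproduces without a refusal step, a flowchart with such a step would disagree with the text.

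A reader might infer more: that the pilot cannot reach 60 per arm, or that a wrong decision against a definitive trial would follow. The documents do not support this. Nothing in them ends recruitment at 900 approaches. The success criterion in the Aim section allows 6 months, while the approach workload is set over 4. At the same pace for 6 months, 300 becomes 450 approaches per arm, and 450 x 0.77 x 0.59 x 0.33 = about 67 recruits per arm, above 60. The Trial Steering Group also monitors progress against projected recruitment. Nor is the gap between 58.4 and 60 a finding in itself.

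**Conclusion.** The point holds as a mislabelled planning denominator. As written, 300 per arm is a number to screen presented as a number to approach. At 77% uptake, the expected yield of 900 approaches is about a quarter below the stated 180 recruits and 90 followed up (135 and 67), and about one third more approaches (1,200) would be needed. The size depends on the assumed uptake and takes the 59%, 33% and 50% as given. Across 70% to 90% uptake, expected recruitment stays below 180, at 123 to 158. No enrolment target, success criterion or analysis is affected. This should be corrected, but it does not undermine the design.

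**What to change.** State the assumed screening uptake and its source, then choose one of two consistent presentations:

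- Relabel 300/900 as arrestees screened, and give about 400 per arm (about 1,200 in total; roughly 1,030 to 1,320 for uptake of 90% to 70%) as arrestees approached. The 400 is for exactly 60 per arm, which means screening 308. Screening 300 would need 300 / 0.77 = about 390 approaches.
- Keep 900 approached, and restate the expected yield as about 135 recruited and 67 at 12 months, with the range.

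At the same time, reconcile the per-site workload with whichever total is kept: 100 per site for 900, or about 133 per site for 1,200, in place of 225. Check that the recruitment flowchart uses the same stages and numbers.

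The cost is a restatement of planning figures. Either the stated number of approaches rises by about a third or the expected yield falls by about a quarter. The target of 60 per arm and the success criteria stay as they are.

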### Financial incentives

Each police custody suite will receive £1,000 to support the delivery of the study and for the burden of the research taking place. Participants in the study will be recompensed for any travel and child care costs incurred as part of the follow-up or qualitative parts of study.

### Training and support

All detention officers or drug and alcohol workers will be trained to deliver interventions by the research team, which has prior experience in the delivery of brief interventions. Training will be delivered as on-site, outreach training. Such outreach training was found to be the most cost-effective implementation strategy for alcohol screening and brief intervention delivery in other settings [34]. Detention officers and drug and alcohol workers will be trained only in the condition to which they are randomised and encouraged not to discuss what they have learned with colleagues. Training will be guided by a written manual and detention officers or drug and alcohol workers will be given a copy of the intervention manual to keep for reference. The training will last around 1 h and will be done either one on one or in a group, depending upon the custody site’s preference, given their time restraints and shift patterns (all these details will be recorded by research staff). Training in intervention 2 for those in the South West will be delivered by the experienced alcohol health worker with responsibility for conducting behaviour change counselling at North East sites and will last around 3 h. In addition to the manualised materials, there will be video-based material of the alcohol health worker delivering key elements of the behaviour change counselling. The session is intended to be highly interactive and will include exercises designed to build core skills including how to assess readiness for change via scaling questions, identify change talk in arrestees and ask open questions that identify motivation for change. The research team will support the staff in implementing study procedures through weekly contact (in person or via telephone) with each police custody suite, and paperwork relevant to the research will be provided by the research team, who will also act as the site study coordinator.

### Qualitative work to explore acceptability and intervention fidelity

A definitive study should only be conducted if the study procedures are found to be acceptable to either detention officers or drug and alcohol workers and arrestees. Thus, a qualitative sub-study will be conducted with a purposive sample of approximately 15–24 arrestees and 8–12 detention officers and/or drug and alcohol workers. In-depth interviews will be guided by a topic guide and will explore the acceptability of the study procedures. Issues relating to consent, the potential for coercion around participation, the alcohol screening process, the timing, content and manner of intervention delivery, the burden of time and how this work is best embedded alongside other activity in the custody setting will be explored with careful prompting where responses seem curtailed. We will also explore intervention fidelity by seeking specific details about the form of intervention that was due to be received or delivered and asking about key elements of the expected intervention. Finally, we will seek views on the ethical aspects of incentivising research participants in this challenging criminal justice setting and if any concerns or contradictions are perceived regarding health care in a criminal justice setting.

We will aim for a maximum variation sample to achieve a broad perspective on the issues being explored. Sampling criteria for arrestees will be age, sex, reason for arrest, study condition and ‘type of drinker’ based on AUDIT category [12]. Sampling criteria for detention officers and drug and alcohol workers will be sex, geographical area, study condition and number of arrestees approached. Emergent issues from earlier interviews will be explored in subsequent interviews and the total number of interviews will be determined by data saturation (no new issues or themes emerging from within/across participants). Interviews with detention officers and drug and alcohol workers will take place after baseline data collection has ceased and will be conducted in a place convenient to the police station. Interviews with arrestees will take place after follow-up data collection has ceased. The venue for interviews with arrestees will be negotiated taking into consideration risk assessment and arrestees convenience, confidentiality and preference. Interviews will last for approximately 45 min each. All interviews will be audio-recorded and transcribed verbatim for analysis.

### Planned analysis

#### Statistical analysis

As this is a pilot feasibility trial, no formal hypothesis is to be tested. The aim of this trial is to provide robust estimates of recruitment, retention and consent rates and provide data for the power calculation of a definitive trial. Descriptive analysis will include participant characteristics (age, sex, educational attainment, social deprivation), numbers and percentages recruited and retained at both follow up points and variability in study measures. In particular, these measures will be considered on an intention to treat basis at 6 and 12 months after the intervention has taken place.

If a definitive trial is judged to be feasible, a decision will be made on the choice of the primary outcome measure. The calculation of sample size for this trial would follow the principles described in the extension of the CONSORT 2010 statement to cluster randomised trials [35] and would take account of several factors, as follows:If the primary outcome measure was continuous, then its standard deviation or (if not normally distributed) the width of its interquartile range based on variability within clusters would be estimated, using the results from the pilot feasibility trial.Alternatively, if the primary outcome measure was dichotomous (e.g. yes/no for the presence of a characteristic), then the sample size calculation would take account of the proportion of participants with this characteristic in the pilot feasibility trial, with adjustment for differences between clusters.The intra-cluster correlation coefficient for the primary outcome measure would be estimated, although—since this is likely to have a large sampling error—alternative values may be used to examine the sensitivity of the calculated sample size to the choice of value.Experience from the pilot feasibility trial about the number of persons who might be recruited per detention officer (or drug and alcohol worker) would also be taken into account, so that a decision could be made about how many clusters are required in a definitive trial.

Health economics assessment will consider costs (training, screening arrestees, delivering interventions, practitioner time) and outcomes (reduced alcohol consumption, reduced problems, re-offending rates).

#### Qualitative analysis

Analysis will be conducted using a structured thematic approach to systematically code, classify and organise interview content into key themes, with the Framework approach employed to organise the analysis [36]. This analytic strategy is characterised by a more deductive than inductive approach and is appropriate for qualitative health research with objectives linked to an applied research question and a delimited time frame. The interview recordings will be reviewed and important or recurrent themes in interviewees’ talk will be identified. These will be combined with a list of key themes of research interest derived from the aims and questions for the study and coded within a framework of a priori headings. Finally, the descriptions of headings within the framework will be compared and the relationships between them elaborated to provide a consistent interpretation of the dataset as a whole [37].

### Ethical and research governance approval

This pilot feasibility trial is funded by NIHR School for Public Health Research and has been assigned the trial reference number ISRCTN89291046. Ethical approval has been granted by Newcastle University (Reference 00754), who will act as sponsor for the research. The trial will be managed through a central co-ordinating team. The Programme Management Group will be responsible for ensuring the appropriate, effective and timely implementation of the trial. A Trial Steering Group will be appointed and will concentrate on the progress of the trial against projected rates of recruitment and retention, adherence to the protocol, participant safety and the consideration of new information of relevance to the research question. Written charters will be agreed and used by both groups.

